### Power calculations

The difference in the expected effect is based on previous research in which 14% of the patients in the intervention group and 28% in the control group were institutionalized [35,36]. We need 132 patient-caregiver dyads for each of the intervention and control groups to detect a 50% reduction in institutionalization rates with 80% power at the two-sided significance level of 0.05. We inflated this sample size with a design effect of 1.15 to 152 dyads for each group to allow for correlating dyads within the same cluster, assuming an average cluster size of four and an intracluster correlation coefficient of 0.05. Assuming a 25% dropout rate of patient-caregiver dyads, the study needed a final enrolment of 190 dyads in each group, so that at least 48 professionals needed to be randomized to each group.

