### Statistical analyses

Analyses will be performed at the level of the caregiver and the patient with dementia. All available data will be analyzed on an intention-to-treat basis, i.e. patient-caregiver dyads will remain in the group to which they are assigned. Descriptive analysis will be used to examine baseline comparability of both the intervention and control groups for sociodemographic characteristics, outcome parameters, and control variables. We will calculate the effect of the SCPD on the primary outcome measure (the number of institutionalizations) with Fisher's exact test. We will use multilevel logistic regression analyses to correct for the design effect of clustering patient-caregiver dyads with the professionals (level 1), and professionals in health services (level 2). We will use Kaplan-Meier survival analysis to quantify the effect of the SCPD on the primary outcome measure, time to institutionalization; and a Cox proportional hazard model, to correct for control variables. Analysis of the effect on the primary outcome and subgroup-analyses – adding the stratifying factor as a covariate and an interaction term of the stratifying factor with treatment group to the models – will be performed for shared household, age, and gender of the caregiver. Random coefficient regression analyses will be used to examine the effect of the SCPD on the secondary outcome measure (the quality of the patient's and the caregiver's lives) and also to correct for the clustering effect of the design, namely, patient-caregiver dyads clustered with professionals (level 1) and professionals in health services (level 2). We will also perform per protocol analyses. Mean substitution will be used for missing values unless at least if two third of the other items of that particular scale was completed. The software SPSS 16.0 (SPSS, Chicago, Illinois) and MLwiN Version 2.0 (Centre for Multilevel Modelling, University of Bristol, Bristol, UK) will be used for all statistical analyses.

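### The 25% dropout allowance was added as 152 × 1.25 instead of 152 / 0.75, so 190 dyads per group give slightly less than the stated 80% power (about 77.5% to 79.3%)

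*Protocol article*

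**What the plan says.** The whole derivation stands in the Power calculations section of the protocol article. The expected effect comes from earlier research in which "14% of the patients in the intervention group and 28% in the control group were institutionalized". The first result is "We need 132 patient-caregiver dyads for each of the intervention and control groups", "with 80% power at the two-sided significance level of 0.05". Clustering comes next: "We inflated this sample size with a design effect of 1.15 to 152 dyads for each group", "assuming an average cluster size of four and an intracluster correlation coefficient of 0.05". The last step is dropout: "Assuming a 25% dropout rate of patient-caregiver dyads, the study needed a final enrolment of 190 dyads in each group". From that enrolment the article derives a minimum of 48 professionals per arm.

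The article does not print the formula for the dropout step, and no other section gives a different dropout figure or derivation.

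**The concern.** The allowance for dropout exists so that the required number of evaluable dyads is still there once the expected losses have occurred. If a quarter of those enrolled are lost, three quarters remain, so the required number must be divided by 0.75. Adding a quarter of the required number gives too small a figure, because the loss is then taken from the larger, enrolled total.

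The enrolment target and the number of professionals to randomise both depend on this step. If it is wrong, the article claims a power that its own dropout assumption does not deliver, and a reader of the results would judge the trial against a figure that is slightly too favourable.

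**Working it through.** **Inputs** (all from Power calculations): 28% and 14% institutionalised; two-sided 0.05; 80% power; equal groups; cluster size 4; intracluster correlation 0.05; dropout 25%.

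**Reproducing the article's figures**

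1. Unadjusted size, pooled normal approximation without continuity correction, with mean proportion 0.21:
n = [1.96 × √(2 × 0.21 × 0.79) + 0.8416 × √(0.14 × 0.86 + 0.28 × 0.72)]² / 0.14² = 131.7, rounded up to 132. This matches.
2. Design effect: 1 + (4 − 1) × 0.05 = 1.15, and 132 × 1.15 = 151.8, rounded up to 152. This matches.
3. Dropout: 152 × 1.25 = 190, which matches. By contrast, 152 / 0.75 = 202.7, which does not.
4. Professionals: 190 / 4 = 47.5, rounded up to 48. This matches.

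So every printed figure reproduces, but the 190 does so only by multiplication by 1.25.

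**What 190 delivers**

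- Evaluable at 25% dropout: 190 × 0.75 = 142.5 per group, which is 9.5 fewer than 152.
- If all 48 professionals enrol four dyads: 48 × 4 = 192, and 192 × 0.75 = 144.
- Dropout at which 190 leaves 152: 1 − 152/190 = 20%.

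**Power**, by the same approximation, with effective n = evaluable dyads / design effect:

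power = Φ{[0.14 × √(effective n) − 1.129] / 0.5675}, where 1.129 = 1.96 × √(2 × 0.21 × 0.79) and 0.5675 = √(0.14 × 0.86 + 0.28 × 0.72).

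The design effect can be read in two ways. If four is the number of dyads analysed per professional, it stays at 1.15. If four is the number enrolled, about three remain after dropout and it becomes 1 + (3 − 1) × 0.05 = 1.10.

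| Evaluable per group | Design effect | Effective n | Power |
|---|---|---|---|
| 152 (as intended) | 1.15 | 132.2 | 80.1% |
| 142.5 | 1.15 | 123.9 | 77.5% |
| 144 | 1.15 | 125.2 | 78.0% |
| 142.5 | 1.10 | 129.5 | 79.3% |
| 144 | 1.10 | 130.9 | 79.8% |

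**Enrolment that would meet 25% dropout**

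- Design effect 1.15: 152 / 0.75 = 202.7, so 203 dyads; 203 / 4 = 50.75, so 51 professionals per group.
- Design effect 1.10: 132 × 1.10 = 145.2 evaluable; 145.2 / 0.75 = 193.6, so 194 dyads; 194 / 4 = 48.5, so 49 professionals per group.

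**The case against.** The strongest defence is that four is a number of enrolled dyads. The article itself divides 190 enrolled dyads by four to get 48 professionals, and the Eligibility criteria section ties the figure of four to the dyads a professional treats each year. Clusters then shrink to about three by the time of analysis, the design effect is 1.10, and the shortfall against 190 is 4 dyads per group (194 − 190), or 2 if 48 professionals supply 192. This largely stands. It means that 203 dyads and 51 professionals are the upper end of a range and not the only right answer. It does not remove the error: power is still below 80%, and the article states a design effect of 1.15.

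A second defence is that dropouts are not wholly lost. Time to institutionalisation also counts towards the primary outcome, and in the Kaplan-Meier and Cox analyses a dyad that leaves early could contribute censored time. That is fair for the time-to-event analysis, but the sample size was calculated for a comparison of proportions.

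A reader might also infer a larger loss from the Statistical analyses section, which says "We will calculate the effect of the SCPD on the primary outcome measure (the number of institutionalizations) with Fisher's exact test". Fisher's test is more conservative than the approximation behind the 132, so one could try to carry its power through the same calculation. The documents do not support this. It would mean applying an unclustered exact test to a sample size deflated for clustering, which no planned analysis does. Fisher's test as planned would use the actual dyads, and the same section names multilevel logistic regression to deal with clustering. No power figure for Fisher's test is part of this point.

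**Conclusion.** The point holds as a minor correction. The dropout step is arithmetically wrong as printed: 25% dropout, 190 enrolled and 152 evaluable per group are inconsistent. With 190 enrolled, power is 77.5% at design effect 1.15 and 79.3% at 1.10; with 192 enrolled it is 78.0% and 79.8%. The loss against 80% is therefore 0.2 to 2.5 percentage points.

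This rests on the article's own rates and intracluster correlation, on the normal approximation that reproduces its 132, and on counting dropouts as contributing nothing to the comparison of proportions.

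A reader might infer that the trial is materially underpowered or that a null result could not be interpreted. The figures do not support that: the gap is small beside the uncertainty in an assumed intracluster correlation and in event rates taken from earlier research.

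**What to change.** Restate the paragraph in Power calculations in one of two ways:

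- keep 190 dyads and 48 professionals per group and say that they allow for 20% dropout (at design effect 1.15); or
- keep the 25% dropout and say that power is then about 77.5% to 79.3%, depending on whether the design effect is 1.15 or 1.10.

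It would help to add whether the cluster size of four means dyads enrolled or dyads analysed, since that decides which end of the range applies.

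If the authors prefer to correct the enrolment figure itself, it is 203 dyads and 51 professionals per group at design effect 1.15 (13 dyads and 3 professionals more than stated), or 194 and 49 at 1.10 (4 dyads and 1 professional more). Further recruitment is not needed to resolve the point. The Study design and setting section describes the professionals as already randomised and the inclusion period in the past tense, so a restatement is the practical course. It costs a sentence or two and a slightly less favourable stated power or dropout allowance. No planned analysis changes.

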### Statistical analyses

Analyses will be performed at the level of the caregiver and the patient with dementia. All available data will be analyzed on an intention-to-treat basis, i.e. patient-caregiver dyads will remain in the group to which they are assigned. Descriptive analysis will be used to examine baseline comparability of both the intervention and control groups for sociodemographic characteristics, outcome parameters, and control variables. We will calculate the effect of the SCPD on the primary outcome measure (the number of institutionalizations) with Fisher's exact test. We will use multilevel logistic regression analyses to correct for the design effect of clustering patient-caregiver dyads with the professionals (level 1), and professionals in health services (level 2). We will use Kaplan-Meier survival analysis to quantify the effect of the SCPD on the primary outcome measure, time to institutionalization; and a Cox proportional hazard model, to correct for control variables. Analysis of the effect on the primary outcome and subgroup-analyses – adding the stratifying factor as a covariate and an interaction term of the stratifying factor with treatment group to the models – will be performed for shared household, age, and gender of the caregiver. Random coefficient regression analyses will be used to examine the effect of the SCPD on the secondary outcome measure (the quality of the patient's and the caregiver's lives) and also to correct for the clustering effect of the design, namely, patient-caregiver dyads clustered with professionals (level 1) and professionals in health services (level 2). We will also perform per protocol analyses. Mean substitution will be used for missing values unless at least if two third of the other items of that particular scale was completed. The software SPSS 16.0 (SPSS, Chicago, Illinois) and MLwiN Version 2.0 (Centre for Multilevel Modelling, University of Bristol, Bristol, UK) will be used for all statistical analyses.

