**Methods and design:**

In our ongoing, cluster, randomized, single-blind, controlled trial, the participants in six mental health services in four regions of the Netherlands have been randomized per service. Professionals of the ambulatory mental health services (psychologists and social psychiatric nurses) have been randomly allocated to either the intervention group or the control group. The study population consists of community-dwelling people with dementia and their informal caregivers (patient-caregiver dyads) coming into the health service. The dyads have been clustered to the professionals. The primary outcome measure is the patient's admission to a nursing home or home for the elderly at 12 months of follow-up. This measure is the most important variable for estimating cost differences between the intervention group and the control group. The secondary outcome measure is the quality of the patient's and caregiver's lives.

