### Outcome parameters

Table 1 presents the types of data used for the outcome parameters:

1. The primary outcome measure is the institutionalizing of the person with dementia in a nursing home during the 12-month follow-up period. Both the institutionalization rate and the time to institutionalization will be taken into account. Possible institutionalization will be assessed every 3 months with one item of the Resource Utilization in Dementia questionnaire[42].

2. The secondary outcome measure is the quality of the caregiver's and the patient's lives. The quality of the caregiver's life will be measured with the Sense of Competence Questionnaire [35], the EuroQol-5D [43,44], the Center for Epidemiologic Studies Depression Scale [45,46], and the caregiver distress will be assessed with the Neuropsychiatric Inventory Questionnaire [47,48]. The patient's quality of life will be measured with the Neuropsychiatric Problems Inventory Questionnaire and the Quality of Life in Alzheimer's Disease [49,50].

Baseline variables as well as sociodemographic characteristics of both the patient and the informal caregiver are control variables. Sociodemographic characteristics are the severity of the patient's dementia according the DSM-III-TR [41], and the caregiver's relation to the patient and their living arrangements. The health service, gender, and job satisfaction [51,52] of the professional are also control variables.

Concerning the effect of the intervention on emotional functioning we expect positive changes on the secondary outcome quality of life – e.g. depressive symptoms, patients' problem behavior and caregiver distress as related to patients' problem behavior, sense of competence, and both caregiver and patient quality of life – at 12 months follow-up, in favor of caregivers and patients involved in the intervention group, as compared to controls.

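### Time to institutionalization is analysed without correction for clustering by professional, and for the rate an uncorrected test stands beside the corrected one with no rule on which decides

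*Protocol article*

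**What the plan says.** The abstract of the Protocol article states that professionals "have been randomly allocated to either the intervention group or the control group", and adds: "The dyads have been clustered to the professionals". The Power calculations section follows this design. It inflates 132 dyads per group to 152, "assuming an average cluster size of four and an intracluster correlation coefficient of 0.05".

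The primary outcome has two parts. Under Outcome parameters: "Both the institutionalization rate and the time to institutionalization will be taken into account". The Hypothesis section gives time to institutionalization an expectation of its own.

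The Statistical analyses section then assigns methods:

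- **Rate:** "We will calculate the effect of the SCPD on the primary outcome measure (the number of institutionalizations) with Fisher's exact test". The next sentence adds multilevel logistic regression, with the stated purpose of correcting for clustering by professional and health service.
- **Time:** Kaplan-Meier, "and a Cox proportional hazard model, to correct for control variables". No frailty term, robust variance or other allowance for the professional is mentioned.
- **Secondary outcomes:** random coefficient models, also with the stated purpose of correcting for clustering.

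**The concern.** When professionals are randomized, dyads seen by the same professional tend to resemble each other, and a treatment comparison that treats them as independent understates its standard error. The plan accepts this when it sizes the trial. It corrects for it in the secondary outcomes and in one of the two rate analyses, but not in the time analysis, which is half of the primary outcome.

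An ordinary Cox model run as described would therefore tend to give a p-value that is too small and an interval that is too narrow. For the rate, the same outcome would yield two p-values, one of them ignoring the design, and nothing says which carries the conclusion. The Policy implications section ties a favourable result to wider implementation, so the error rate of the primary comparison matters.

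**Working it through.** **Inputs (Power calculations, Protocol article).** "14% of the patients in the intervention group and 28% in the control group were institutionalized"; two-sided alpha 0.05; power 80%; cluster size m = 4; ICC = 0.05.

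**1. Reproduce the plan's figures.** Two-proportion formula with pooled variance under the null, mean rate 0.21:

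- n = [1.96·√(2·0.21·0.79) + 0.8416·√(0.28·0.72 + 0.14·0.86)]² / 0.14² = (1.129 + 0.478)² / 0.0196, about 132 per group.
- Design effect = 1 + (4 − 1)·0.05 = 1.15, and 132·1.15 = 151.8, rounded to 152.

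Both stated figures are reproduced.

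**2. Cost of ignoring the clusters at the plan's inputs.**

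- True standard error / naive standard error = √1.15 = 1.072. Correct intervals are about 7% wider.
- True alpha = 2·[1 − Φ(1.96/√1.15)] = 2·[1 − Φ(1.828)] = 0.0676.

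**3. Check by simulation under the null.** Beta-binomial clusters, 38 clusters of 4 per arm (152 dyads), ICC 0.05, overall event rate 21% or 28%. The log-rank test stands in for an unadjusted Cox model, whose score test it is.

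| Test | ICC 0 | ICC 0.05 |
|---|---|---|
| Log-rank | 4.9% | 6.7% to 6.8% |
| Fisher's exact | 3.5% | 5.1% to 5.5% |
| Cluster-level t-test | 4.7% to 4.9% | 5.0% to 5.5% |

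Fisher's exact test is conservative without clustering, and that offsets most of the inflation. Other simulations with 48 professionals per arm gave 4.9% (no dropout) and 5.5% to 5.8% (25% dropout).

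**4. How far the figure moves.** The documents do not settle any of these inputs, so all are assumptions.

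- *ICC, with m = 4:* 0.02 gives 5.7%; 0.10 gives 8.6%.
- *Smaller clusters:* if dropouts contribute nothing and m falls to 3, the design effect is 1.10 and alpha 6.2%.
- *Larger clusters:* the eligibility criteria require at least four dyads a year, and inclusion lasted 17 months. At that minimum rate throughout, m = 4·17/12 = 5.7, the design effect is 1 + 4.7·0.05 = 1.23 and alpha about 7.8%.
- *Part of the ICC between health services:* the abstract describes randomization per service, which I read as within each service. Service effects then balance across arms, and the variance ratio is (1 − 0.05) + 4·(professional part of the ICC). With the ICC split evenly this is 0.95 + 0.10 = 1.05, alpha 5.6%. With all of it between services it is 0.95, alpha 4.4%.

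**The case against.** **An article condenses the plan, and a frailty term or robust variance could stand in an analysis plan that is not shown.** This would carry weight if the section were silent on clustering. It is not: it gives each method a purpose, names clustering for the logistic and random coefficient models, and names something else for Cox.

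**Other sections might supply the correction.** They do not. Health service and the professional's gender and job satisfaction are control variables under Outcome parameters, but such covariates do not model the correlation that remains within a professional. The multilevel models under Process evaluation that include time to institutionalization concern delivery of the program as planned, not the randomized comparison. The Economic evaluation says its effect analysis will respect the cluster design, but gives no method.

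**The 6.8% is near the top of the range at the planned ICC and cluster size.** This stands. Between-service correlation would lower it, and the planned Cox model is adjusted, so the log-rank figure is a proxy. Kaplan-Meier curves are not biased by clustering; only their variance is affected.

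**The rate is already corrected.** This also stands. A reader might infer from the Fisher sentence that the rate result will be invalid. The next sentence plans a cluster-corrected model, and Fisher's size at the planned inputs is near 5%.

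**Ties.** A reader might also infer from "Possible institutionalization will be assessed every 3 months with one item of the Resource Utilization in Dementia questionnaire" that event times will be heavily tied and a Cox model unsuitable. The documents do not show whether admission dates are recorded at those contacts, and standard corrections for ties exist. The 3-month schedule makes a discrete-time model a reasonable option, not a necessity.

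**Conclusion.** The time analysis is wrong as written: a cluster-randomized comparison of a primary outcome has no stated allowance for clustering by professional. At the plan's own design effect of 1.15, the true two-sided alpha is up to about 6.8% instead of 5%, and intervals are about 7% too narrow. This assumes that the ICC of 0.05 applies to the time outcome and lies between professionals. The error is modest; how far it departs from this figure depends on the actual ICC, where it lies and the cluster sizes.

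For the rate the conclusion is narrower. Valid inference is planned, but an uncorrected test is the one named to calculate the effect, and no rule says which result decides. The documents do not support a claim that all primary p-values are wrong, or that Fisher's test materially exceeds 5% at the planned inputs. Its protection comes only from its conservatism and should not be relied on: in simulation it reaches about 7% at an ICC of 0.10.

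**What to change.** In the Statistical analyses section:

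- Add a shared frailty or a cluster-robust variance by professional to the Cox model. Alternatively, use a discrete-time multilevel hazard model on the 3-month intervals with a random effect for the professional. That is a multilevel model for a binary response, so the multilevel software already named should serve.
- Keep Kaplan-Meier curves for description, and base any test of the difference between them on the cluster-corrected model.
- Name the multilevel logistic model as the analysis that decides the rate.
- Label Fisher's exact test descriptive, or drop it.

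No new data are needed. The cost is a few sentences, a little more analysis work and slightly wider intervals, about 7% for the time analysis at the planned design effect.

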### Ethical principles

The Committee on Research Involving Human Subjects, Arnhem-Nijmegen Region, approved the study protocol on March 9, 2005. Participation in the study is voluntary. Written consent must be obtained from all participating informal caregivers (see the section *Informed consent procedure*). Informal caregivers must explicitly be informed about the fact that they can withdraw their consent any time, without any specific reason, and with no negative consequences with regard to healthcare treatment now or in the future. Patient-caregiver dyads who withdraw from the study will continue to receive treatment from the professional they are assigned to. If a patient is institutionalized, or has died, the caregiver will no longer be invited to follow-up appointments.

Professionals from the health services allocated to the control group will not receive the SCPD training during the trial. However, they will be offered such training after the trial. This means that they can enter the SCPD, but with a 12-month delay.

Names of patient-caregiver dyads and other confidential information will be treated with medical confidentiality, and data are always separated from the names of the patient-caregiver dyads. Each participant is identified in the database by a number and an identity code. These codes are available only to the investigators and the research assistant.

The target groups are people with dementia, their informal caregivers, caregiver organizations, Alzheimer societies, professional healthcare workers, researchers of dementia care, and policy makers. The results of and information about the SCPD will be disseminated in publications and presentations at scientific and professional conferences and directly to family caregivers in Alzheimer cafes. The health services will also spread the results through their regional contacts.

